***MAIN ELIGIBILITY CRITERIA***

***DISEASE CHARACTERISTICS:***

• Histologically confirmed colon or rectal adenocarcinoma.

• Resectable or resected metastatic disease (liver, lung, ovary or peritoneum).

• Only one metastatic site will be allowed.

• Patients with peritoneum metastasis in case of single and completely resected metastasis.

• Radiofrequency ablation, alone or in combination with surgical resection, will authorized provided no more than 3 liver metastases with a maximum diameter <35 mm.

• Prior adjuvant chemotherapy after resection of the primary tumor will be allowed if the interval between the end of chemotherapy and relapse will be ≥12 months.

***PATIENT CHARACTERISTICS***:

• Age 18-75,

• Alkaline phosphatase ≤5 x upper limit of normal (ULN),

• Aspartate and alanine transaminases ≤3x ULN,

• Neutrophil count ≥2.0x109/L,

• Platelet count ≥100x109/L,

• Bilirubin ≤2 times normal,

• Creatinine ≤135 µmol/L or creatinine clearance ≥ 60mL/min,

• No peripheral neuropathy that affects normal functions,

• No unresolved complications from prior surgery,

• WHO performance status ≤2,

• Adequate hematologic, renal and liver functions.

***PRIOR OR CONCURRENT THERAPY:***

• At least 1 year since prior FOLFOX4 or FOLFIRI regimen in the adjuvant setting.

• No concurrent participation in another clinical trial.

• Recovered from prior therapy.

**RANDOM ASSIGNEMENT AND STRATIFICATION**

• Random assignment will be centralized and performed using an Interactive Voice Response System.

• Stratifying by:

- Treatment chronology (perioperative *vs.* postoperative chemotherapy),
- Type of local therapeutic intervention (surgery *vs.* radiofrequency ablation +/- surgery,
- Blumgart’s score (0-1 *vs.* 2-3 *vs.* 4-5).

**MAIN NOT EGLIBITITY CRITERIA**:

• Patients who have previously received chemotherapy for metastatic disease,

• Unresolved postoperative complication, or prior chemotherapy in the metastatic setting,

• Presence of cirrhosis,

• Presence of extrahepatic metastases or metastatic foci after radical treatment,

• Macroscopically incomplete resection of liver metastases,

• Pulmonary embolism or stroke within 6 months prior to entry into the study,

• Peripheral sensory neuropathy with functional impairment,

• Evidence of other diseases or medical conditions within 6 months prior to study,

• Patients participating in another study,

• Patients who cannot be monitored regularly,

• Pregnant of breast feeding woman.

**PROJECTED ACCRUAL**:

• A total of 284 patients, 142 per treatment arm.

**ENDPOINTS EVALUATION**

• DFS defined as the interval between randomization and first evidence of relapse (local, regional, metastases or second CRC), or death from any cause.

• OS defined as the interval between randomization and patient death from any cause.

• Toxicity assessed according to the National Cancer Institute Common Toxicity Criteria (NCI-CTC) criteria, version 2.0.

• Tumor response (complete response, partial response, stable disease, progressive disease), ORR and disease control rate assessed according to the RECIST 1.0 criteria.

• HRQoL assessed using the European Organization for Research and Treatment of Cancer (EORTC) self-administered Quality of Life Questionnaire (QLQ-C30) at baseline and at 8, 16 and 24 weeks.

• Time until definitive deterioration (TUDD) used for longitudinal analyses defined as the interval between randomization and the first observation of a definitive deterioration of QLQ-C30 score, the later including 5 points decrease in QoL score compared to the QoL score at baseline, no improvement in QoL score ≥5 points as compared with baseline or patient drop-out after ≥5 points decrease resulting in missing data or death.

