**OBJECTIVES**:

***Primary***

• 2-year disease-free survival (DFS) rate.

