***Secondary***

• Overall survival (OS).

• Toxicity (according to the National Cancer Institute Common Toxicity Criteria, version 2.0).

• Health-related quality of life (HRQoL).

• Objective response rate (ORR).

• In case of perioperative chemotherapy:

- Tumor response according to the RECIST 1.0
- Resection type (R0 vs. R1 vs. R2).

• Postoperative complication rate.

• Transfusing rate in patients having metastasis surgery.

• Pharmacogenetics.

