**TREATMENT PLAN:**

Patients will be randomized to 1 of 2 treatment arms:

•Arm I (12 cycles of FOLFOX 4): Patients will receive FOLFOX 4 chemotherapy comprising leucovorin 200 mg/m2 by infusion over 2 hours on days 1- 2, oxaliplatin 85 mg/m2 by infusion over 2 hours on day 1, fluorouracil 400 mg/m2 over 15 min on days 1- 2, then fluorouracil 1200 mg/m2 over 46 hours. Treatment will repeat every 2 weeks for 12 courses in the absence of disease progression or unacceptable toxicity.

•Arm II (6 cycles of FOLFOX 7 and FOLFIRI): Patients will receive 6 cycles FOLFOX 7 combination chemotherapy comprising high-dose oxaliplatin 130mg/m2 infusion on day 1 in combination with leucovorin 200 mg/m2 by infusion over 2 hours followed by fluorouracil 2400 mg/m2 by continuous infusion over 46 hours followed by 6 cycles of FOLFIRI consisted of irinotecan 180 mg/m2 by 30-90 min infusion in combination with leucovorin 200 mg/m2, fluorouracil 400 mg/m2 over 15 min on day 1, followed by fluorouracil 2400 mg/m2 over 46 hours. Treatment will repeat every 2 weeks for 6 courses in the absence of disease progression or unacceptable toxicity.

Simple or complex surgical procedures will be authorized, provided resection will be complete or considered to be initially feasible in case of preoperative chemotherapy. Patients who will undergo R2 (residual tumor) resection will be taken off the study. In patients operated before the entry into the study, a R0 resection will be required.

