**STATISTICAL ANALYSIS:**

***POWER OF TRIAL AND CLINICAL JUSTIFICATION***

• According to hypothesis that the 2-year DFS might be improved from 30% with FOLFOX4 chemotherapy to 45% with FOLFOX7-FOLFIRI (Hazard Ratio [HR] of 0.66), 15% difference using a 80% power and bilateral α type I error of 5%, 188 events is required. Based on estimated 36 months inclusion duration, and 24 months follow-up, at least 248 patients has to be enrolled. Assuming a drop-out rate around of 20% (disease progression before surgery, R2 resections or lost to follow-up), a total number of 284 patients, 142 per treatment arm, will be required.

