***ANALYSIS OF EFFICACY*** ***AND SAFETY***

• Performed on all randomized patients who will receive at least one dose of chemotherapy with a use of a modified Intent-to-Treat (mITT) approach.

• Survivals and median follow-up will be estimated by the Kaplan-Meier and reverse Kaplan-Meir methods.

• Response rate will be presented with corresponding 95% CI for the median.

• Treatment outcomes will be compared using a log-rank test.

• Proportional hazard assumptions will be based on Schoenfeld residuals.

• TUDD will be evaluated using the Kaplan-Meier method.

**REASONS FOR EARLY CESSATION OF TRIAL:** Not applicable.

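### In perioperative patients, progression before surgery and R2 resection are budgeted as drop-out and are not listed as DFS events, so failures that treatment can affect go uncounted when they occur

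*Protocol*

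**What the plan says.** The primary objective is the "2-year disease-free survival (DFS) rate". Under Endpoints evaluation the Protocol gives "DFS defined as the interval between randomization and first evidence of relapse (local, regional, metastases or second CRC), or death from any cause".

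Four other places bear on how an early failure is handled:

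- **Random assignment and stratification** stratifies by "perioperative *vs.* postoperative chemotherapy". Perioperative patients therefore start study chemotherapy after randomization with their metastases unresected. The Treatment plan requires R0 resection at entry only for patients operated on beforehand.
- **Treatment plan**: "Patients who will undergo R2 (residual tumor) resection will be taken off the study".
- **Power of trial and clinical justification**: "Assuming a drop-out rate around of 20% (disease progression before surgery, R2 resections or lost to follow-up", given as the reason for raising 248 patients to 284. The design effect is that "the 2-year DFS might be improved from 30% with FOLFOX4 chemotherapy to 45% with FOLFOX7-FOLFIRI (Hazard Ratio [HR] of 0.66".
- **Analysis of efficacy and safety**: "Performed on all randomized patients who will receive at least one dose of chemotherapy", called a modified intention-to-treat approach.

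Among the secondary objectives for perioperative patients is "Resection type (R0 vs. R1 vs. R2".

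**The concern.** DFS starts at randomization, but its event list suits a patient who has already been cleared of disease. A perioperative patient whose metastases progress before surgery, or whose resection leaves residual tumor, was never disease-free, and relapse is not a natural word for that outcome. These are among the clearest treatment failures in the trial. They arise after randomization, and the arms may differ in them; the plan itself makes tumor response and resection type outcomes in these patients.

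If such patients are censored when they leave the study, or left out, the censoring is informative and the primary comparison becomes one among patients who were successfully resected. An effect of the dose-dense regimen on reaching resection, in either direction, would then be missing from the primary endpoint. Ending follow-up of R2 patients would also cost overall survival data.

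**Working it through.** **1. The provisions side by side.**

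- *Event list:* relapse or death. Progression before surgery and R2 or unresectable outcome are absent.
- *Drop-out list:* progression before surgery, R2 resection, loss to follow-up. A patient who supplies a DFS event contributes information and needs no inflation. Inflating for these two groups shows that the design treats them like patients lost.
- *Off-study rule:* explicit for R2 only.
- *Analysis set:* all treated patients. This fixes who is analysed, not which outcome is an event or on what date.

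**2. The plan's own event figure.** Inputs: HR 0.66, two-sided 5%, 80% power. Freedman's formula gives events = (1.960 + 0.842)² × [(1 + 0.66)/(1 − 0.66)]² = 7.849 × 23.84 = 187.1, rounded up to **188**, as stated. The HR agrees with the rates: ln 0.45 / ln 0.30 = 0.663.

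**3. How many patients could be affected.** The document gives neither the size of the perioperative stratum nor the failure share within it. It gives two ceilings, both of which also contain loss to follow-up:

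- 20% of 284 = 56.8, about 57 patients (28.4 per arm);
- 284 − 248 = 36 patients, and 36/284 = 12.7%.

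That 248, 20% and 284 do not fit together is a separate matter and does not decide this point.

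**4. Illustration, equal shares.** Assume that 30% and 45% describe the patients without such a failure, and that a share q of each arm fails early. Counting those failures, 2-year DFS = (1 − q) × 30% and (1 − q) × 45%. The HR equivalent is the ratio of the logs of the two rates, and the required events come from Freedman's formula.

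| q | Control | Experimental | Difference (points) | HR equivalent | Events required |
|---|---|---|---|---|---|
| 5% | 28.5% | 42.8% | 14.3 | 0.68 | 212 |
| 10% | 27.0% | 40.5% | 13.5 | 0.69 | 234 |
| 20% | 24.0% | 36.0% | 12.0 | 0.72 | 287 |

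The last two columns are rough, because a cluster of early failures would not give proportional hazards.

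**5. Illustration, unequal shares.**

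- 10% control, 20% experimental: 0.90 × 30% = 27.0% and 0.80 × 45% = 36.0%; difference **9.0 points**.
- 20% control, 10% experimental: 0.80 × 30% = 24.0% and 0.90 × 45% = 40.5%; difference **16.5 points**.
- Leaving these patients out: 30% and 45%, **15 points** in both cases.

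**6. Would 284 patients supply enough events?** Assume uniform accrual over 36 months, 24 further months of follow-up, exponential DFS and no loss to follow-up. The event probabilities are then 0.861 and 0.738, mean 0.799. Expected events = 284q + 284(1 − q) × 0.799, which is about 230, 233 and 238 for q = 5%, 10% and 20%. Against step 4 this is enough at 5%, about even at 10% and short at 20%.

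**7. The other reading of the design rates.** If 30% and 45% already count these failures, the 188 events stand and no inflation for these patients is needed. The document does not say which reading applies.

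**The case against.** The strongest reply is that no sentence tells the analyst to censor or exclude these patients. The drop-out parenthesis is a sample-size allowance, not an analysis rule. The only stated analysis set keeps everyone who received a dose, and a patient can be off study yet still be analysed on the data collected. Death from any cause remains an event, and detailed event and censoring rules are often left to a statistical analysis plan, which is not shown here.

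Much of this stands, and it rules out several stronger readings that a reader might infer:

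- *Both groups are taken off the study.* The text says so only for R2. For progression it makes continued treatment conditional on its absence and, in the sample-size paragraph, calls it drop-out.
- *The plan orders these patients to be ignored.* That follows only from combining the event list, the drop-out list and the off-study rule. Later deaths would count, but only if follow-up continues.
- *The analysis set flatly contradicts the off-study rule.* The two can coexist; what is unclear is what leaving the study means for follow-up and event status.
- *A fifth of each arm fails this way.* The 20% is a ceiling that includes loss to follow-up, and the problem arises only in the perioperative stratum.

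The reply still does not remove the point. The event list and the drop-out list are written in the Protocol, so an analysis plan that counted these failures would depart from both. Nor can an analysis plan recover follow-up that has stopped.

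**Conclusion.** The point holds for the perioperative stratum. Followed as written, the Protocol does not count progression before surgery or R2 resection as DFS failures when they occur. Two analysts could derive different primary results from the same patients, and the reading that best fits the sample-size paragraph is the one exposed to bias.

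The size is unknown. The failure shares in the illustrations are assumed, and the rates rest on 30% and 45% describing the remaining patients. On that basis equal shares of 5% to 20% shrink the 15-point target to between 14.3 and 12.0 points, and a 10-point imbalance between arms moves the true difference to 9.0 or 16.5 while an analysis without these patients still shows 15. The direction depends on which arm fails more, which the document cannot tell us; it would be wrong to conclude that the plan favours either arm. Because the primary endpoint is affected, the definition should be settled in the Protocol.

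**What to change.** - **Endpoints evaluation:** add to the DFS events progression before surgery, at its date, and an unresectable or R2 outcome, at the date of surgery or of the decision.
- **Treatment plan:** state that R2 patients remain in DFS and overall survival follow-up and in the analysis. No treatment rule needs to change.
- **Power of trial:** limit the drop-out allowance to loss to follow-up. State whether 30% and 45% include these failures; if they do not, restate the event figure or the power.

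The cost is modest but goes beyond wording. The scan schedule and resection type are already in the plan, but R2 patients must be followed further. Reported 2-year DFS will be lower in both arms, and the stated power may become less favourable if the design rates exclude these failures.

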**TREATMENT EVALUATION**

• Thoracic CT scan and abdominal CT or MRI scans will be performed within two weeks before inclusion.

• In patients who will undergo preoperative chemotherapy abdominal CT-scan will be repeated before surgery.

• Positron emission tomography scan is optional, while intra-operative ultrasound is recommended.

• MRI or CT-scans and carcinoembryonic antigen assay will be performed at baseline, before surgery and at the end of chemotherapy.

• Examinations will be repeated every 3 months for 2 years, and every 6 months thereafter.

**STATISTICAL ANALYSIS:**

***POWER OF TRIAL AND CLINICAL JUSTIFICATION***

• According to hypothesis that the 2-year DFS might be improved from 30% with FOLFOX4 chemotherapy to 45% with FOLFOX7-FOLFIRI (Hazard Ratio [HR] of 0.66), 15% difference using a 80% power and bilateral α type I error of 5%, 188 events is required. Based on estimated 36 months inclusion duration, and 24 months follow-up, at least 248 patients has to be enrolled. Assuming a drop-out rate around of 20% (disease progression before surgery, R2 resections or lost to follow-up), a total number of 284 patients, 142 per treatment arm, will be required.

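### The 248 patients, the drop-out rate of about 20% and the total of 284 do not follow from one another, and 248 is itself not reproduced from the stated inputs

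*Protocol*

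**What the plan says.** The section Power of trial and clinical justification assumes that "the 2-year DFS might be improved from 30% with FOLFOX4 chemotherapy to 45% with FOLFOX7-FOLFIRI", gives this as "Hazard Ratio [HR] of 0.66", and sets 80% power with a two-sided 5% error. From this it concludes that "188 events is required". With 36 months of inclusion and 24 months of follow-up, "at least 248 patients has to be enrolled". The last step reads: "Assuming a drop-out rate around of 20% (disease progression before surgery, R2 resections or lost to follow-up), a total number of 284 patients". The section Projected accrual repeats the total: "A total of 284 patients, 142 per treatment arm".

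Three other sections bear on what drop-out means here:

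- Analysis of efficacy and safety uses a modified intent-to-treat (mITT) set of all randomized patients who received at least one dose of chemotherapy.
- Endpoints evaluation runs DFS from randomization to relapse, second colorectal cancer or death from any cause.
- Treatment plan takes patients with an R2 resection off the study.

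**The concern.** A reader who applies the stated drop-out rate to the stated patient number does not reach the stated total by any usual formula. All three figures are fixed in the Protocol's running text, and 284 appears in two sections, so this is neither a detail left to the SAP nor an extraction fault.

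At stake is the justification of the trial's size for its primary endpoint. As written, nobody can tell how many patients are expected to inform the DFS comparison, how many events they should yield, or what power the 284 were meant to secure.

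**Working it through.** **Inputs**, all from Power of trial and clinical justification: two-sided α 0.05, power 0.80, 2-year DFS 30% and 45%, HR 0.66, 188 events, 36 months' accrual, 24 months' follow-up, 248 patients, drop-out about 20%, total 284 (1:1).

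**1. Events: reproduced.**
- ln 0.45 / ln 0.30 = 0.663, which agrees with the stated 0.66.
- Freedman: (1.96 + 0.842)² × [(1 + 0.66)/(1 − 0.66)]² = 7.849 × 23.84 = 187.1, rounded up to an even 188. This is the plan's figure.
- Schoenfeld at HR 0.66 gives 182.

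**2. Patients before drop-out: not reproduced.** Assumptions: exponential DFS, uniform accrual over A = 36 months, and F = 24 months of follow-up after the last inclusion.
- Event probability = 1 − [exp(−λF) − exp(−λ(A+F))]/(λA).
- Control: λ = −ln 0.30/24 = 0.0502, probability 0.861.
- Experimental: λ × 0.66, probability 0.736. The mean is 0.799.
- 188/0.799 = 235.4, so 236 for equal arms, against the stated 248.
- Conversely, 248 × 0.799 = 198 events, not 188. A figure of 248 would fit about 19 months of minimum follow-up.
- If 24 months were instead a fixed observation time per patient, the mean probability would be 0.624 and 188/0.624 about 302. That does not give 248 either, and Treatment evaluation continues examinations beyond two years.

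**3. Drop-out step: not reproduced.**
- 248/(1 − 0.20) = 310.
- 248 × 1.20 = 297.6, so 298.
- 1 − 248/284 = 12.7%. As an add-on, 284/248 − 1 = 14.5%.
- 284 × 0.80 = 227.2, so 227 patients, 21 below 248.
- The one route found from 20% to 284 is 236 × 1.20 = 283.2, rounded up to 284. It starts from the recomputed 236, not from the stated 248.

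**4. Worst case for events and power.** Assumptions: all 20% contribute no event, follow-up stays as planned, HR 0.66. Power (Freedman) = Φ[√events × (1 − HR)/(1 + HR) − 1.96]; power (Schoenfeld) = Φ[√events × |ln HR|/2 − 1.96].

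| Event fraction | Events from 227 | Freedman | Schoenfeld |
|---|---|---|---|
| 188/248 = 0.758 (the plan's ratio) | 172 | 76.7% | 77.8% |
| 0.799 (step 2) | 181 | 78.8% | 79.9% |

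For comparison, 188 events give 80.2% (Freedman) or 81.3% (Schoenfeld). With the unrounded HR of 0.663 the second row becomes 181.6 events, and its powers fall by about one point (77.9% and 79.0%).

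**5. If drop-outs are censored rather than removed.** Assumption: 20% are lost gradually, by some point between 24 and 60 months. Then 284 patients give about 198 to 215 events and 82% to 85% power (Freedman).

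**The case against.** The strongest counter-argument is that the mismatch may have no consequence. A reader might infer from 227 against 248 that the trial will miss 188 events and 80% power. The Protocol does not support that. It would require every drop-out to contribute neither an event nor follow-up time, and follow-up to stop as planned. The mITT rule excludes nobody for progression before surgery, R2 resection or loss to follow-up once a dose has been given. A patient lost to follow-up is ordinarily censored in a log-rank analysis, not deleted.

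The break-even is modest. Of the 57 drop-outs (284 − 227), 16 events (28%) would restore 188 from 172, and about 7 (12%) would restore it from 181. About five more months of follow-up (29 instead of 24) would also bring 227 patients to 188 events. The drop-out rate is itself given only as approximate.

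All of this stands, and it limits the consequence. It does not repair the paragraph: an approximate 20% does not stretch to 12.7%. One uncertainty also remains. Patients with R2 resection leave the study, so their later follow-up is unclear even though the mITT rule keeps them in the analysis set.

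**Conclusion.** The sample-size paragraph is wrong as written: 248, about 20% and 284 cannot all stand. Which of them is at fault cannot be decided from the document. Two tempting conclusions go too far:

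- That 310 is the correct size. This holds only if 248 and 20% are both right, and 248 is not reproduced.
- That the true allowance was 12-13%. This is back-fitted from 248. The match of 236 × 1.2 with 284 points elsewhere, although that too is inference and is not shown in the Protocol.

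The possible loss is 0 to about 3 points of power (77-80% at HR 0.66, about 172 to 182 events), and only if drop-outs contribute nothing and follow-up is fixed. It may be nil if treated drop-outs are censored or counted as events. The figures rest on exponential DFS, uniform accrual and 24 months read as minimum follow-up. Because the effect is small and conditional, this should be fixed but is not critical.

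**What to change.** Keep 284 and rewrite the paragraph so that the patient number before drop-out, the drop-out rate and the total follow from one another:

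- **Patient number before drop-out.** Show how it comes from 188 events, the accrual period and the follow-up. If 248 stands, give the assumptions that produce it. If the base was about 236, say so.
- **Inflation.** State the formula. Multiplying by 1.2 allows for a loss of 1 − 1/1.2 = 16.7%, not 20%.
- **Drop-out.** Say whether each listed group is excluded, censored or counted as a DFS event, in line with the mITT rule. That rule keeps treated patients with progression before surgery or R2 resection in the analysis. Base the allowance on those who really contribute less information, and reconcile it with the statement that R2 patients leave the study.
- **Expected yield.** Restate expected events and power for 284. If 20% are to contribute nothing, this means about 227 patients, 172 to 182 events and 77-80% power.

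Do not simply relabel the drop-out rate as 12-13%, because that leaves 248 unexamined. The cost is one corrected paragraph and no extra patients. The downside is that the stated power may fall by up to about 3 points.
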